### Objectives and hypotheses

The primary objective of this study is to assess whether the ENGAGE-MUSIC/SPANISH program leads to cognitive gains in episodic memory at the immediate follow-up assessment in older adults with a subjective memory complaint when compared with an active control condition. The secondary objectives of this study are: to assess whether these cognitive gains are maintained at the 24-month follow-up; to determine the effect of the program on attentional control, psychological health, activities of daily living, and brain structure and function as measured by magnetic resonance imaging (MRI); and to identify if the characteristics of participants modulate outcomes. Finally, the study will examine whether music and Spanish lessons produce different effects on the primary and secondary outcome measures.

It is expected that the ENGAGE-MUSIC/SPANISH training will show evidence of efficacy: persons enrolled in the ENGAGE-MUSIC/SPANISH training program will have larger gains in the memory composite measure following training than participants enrolled in the active control condition. Secondary hypotheses involve maintenance of training gains, and effects of training on attentional control, daily functioning, well-being, and brain structure and function. It is hypothesized that training effects on the memory composite will be maintained at the 24-month follow-up assessment. As the ENGAGE-MUSIC/SPANISH program includes a component of attention training, it is expected that measures of attentional control will improve. It is also expected that cognitive improvement will transfer to measures of activities of daily living (e.g., managing finances, medication, grocery shopping) and that it will increase indicators of psychological health. Also, the ENGAGE-MUSIC/SPANISH training will result in measurable effects on the brain as assessed by both structural (cortical thickness and regional grey matter volume) and task-related MRI activation, and that these changes will be correlated with improved cognition. Finally, we hypothesize that participant characteristics (sex, age, education) will modulate efficacy and transfer.

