**Fig. 1 Fig1:**
[figure not shown]
Illustration of the study design. *ADCS-ADL-PI* Alzheimer’s Disease Cooperative Study—Activities of daily living—Prevention Instrument; *CLSA* Canadian Longitudinal Study on Aging; *(f)MRI* (functional) magnetic resonance imaging; *V0* Phone screening interview; *V1* First visit (screening); *V2* Second visit (clinical assessment); *V3* Third visit (neuropsychological assessment); *V4* Fourth visit (neuropsychological assessment); *V5* Fifth visit (MRI; includes fMRI for a subgroup of participants); *V6-29* ENGAGE Intervention sessions (24 visits); *V30* 4-month follow-up neuropsychological assessment; *V31* 4-month follow-up MRI/fMRI (for a subgroup of participants); *V32 & V34* 24-month follow-up neuropsychological assessment; *V33* 24-month follow-up clinical visit; *V35* 24-month follow-up MRI. X: administered during the visit; ♦: given to be completed at home by next visit

Participants will be randomly assigned to one of two conditions: the intervention program combining stimulating leisure activities with formal cognitive training (ENGAGE-MUSIC/SPANISH) or an active control condition (ENGAGE-DISCOVERY). As the program is based on the notion that leisure activities are pleasant, and because some people may have strong discomfort with learning music or be reluctant to learn foreign languages, participants will have the option of excluding either the “Music” or “Spanish” activity at their entry in the study. Participants randomized in the intervention (ENGAGE SPANISH/MUSIC) arm who did not exclude one activity will receive either Spanish or music training based on a second independent random assignment. Thus, the intervention versus active control comparison is fully randomized, but secondary analyses comparing the two leisure activities will rely on a partially randomized cohort. Furthermore, and as described below, analyses will first compare the fully randomized cohorts followed by a comparison of the comprehensive cohort, including those in the preference arms.

For all three groups (ENGAGE-MUSIC, ENGAGE-SPANISH, and ENGAGE-DISCOVERY) 24 training sessions will be delivered over a 4-month period. Participants will be assessed at baseline, which will be no more than 8 weeks prior to training (PRE), at 4-month follow-up, i.e., no more than 4 weeks following training (F4), and 24 months after baseline (F24).

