### Randomization and blinding procedure

The opportunity to exclude either music or Spanish training will be offered to all participants prior to randomization. Randomization will be done individually (i.e., one participant at a time as they enter the study) with random lists of binary numbers. Lists will be generated using the Random.org online software. Randomization will be controlled by a person from the Montreal site who is independent of the study. A first randomization will allocate participants to the intervention or control condition by matching the sequential list of participant identification codes with the list of random condition allocation. This will be done with a 2 to 1 ratio between intervention and control conditions. A second randomization will be used to allocate participants in the intervention condition to either Spanish or music training, using a 1 to 1 ratio for participants who did not exclude either of these two activities. Participants randomized in the intervention condition who excluded music or Spanish training will be placed in their preferred activity. Recruiting staff will contact (via telephone) the trial allocation office in charge of randomization once a participant has consented to participate and will be given the allocation. The allocation and sequence of allocation will be concealed from evaluators.

Evaluators who will be assessing the participants will be blinded to the hypotheses and to the group assignment of participants. Participants will be asked not to mention their group assignment to evaluators. Any breach of this group assignment blinding by participants will be noted, but since evaluators will be blinded from the hypotheses this should have minimal effect on integrity. Activity leaders will not be blinded to the study hypotheses. Although participants will know that they are in the Spanish, music, or documentary discussion group, they will not be informed of the study hypotheses, i.e., participants assigned to ENGAGE-DISCOVERY will be unaware that it is an active control condition. To keep participants blinded from the hypotheses and reduce the likelihood that the expectations of participants bias the data [29], close attention will be paid to ensure that the content of the intervention and the wording of recruitment documents and consent forms do not convey the expectations that one condition is inferior in terms of its effect on the brain and cognition.

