#### Analysis of efficacy and maintenance on primary and secondary outcomes

Descriptive statistics will be used for demographics and baseline characteristics, with means and standard deviations given. We will compare the intervention groups on these variables using one-way analysis of variance (ANOVA) for continuous variables and Chi-square analyses for discrete variables. The primary efficacy analysis will be done with a modified intention-to-treat approach retaining all participants and identifying the characteristics of participants withdrawing from follow-up as well as the causes for withdrawal. As proposed for preference trials, a first set of analyses will only use fully randomized participants. This will be followed by analyses of the comprehensive cohort which will include those in the preference arms.

The linear mixed model will be used to assess the efficacy of the intervention. The mixed linear model has many advantages over typical ANOVA; it handles correlated data and is robust to unbalanced design, hence allowing for the inclusion of all participants, including those missing at follow-up. Missing data will not be imputed as mixed models use all available data, including those from participants having incomplete follow-up. The fixed effects will be intervention (ENGAGE SPANISH/MUSIC versus ENGAGE DISCOVERY), time (PRE versus F4), and their interaction. A significant interaction is expected if the intervention is more beneficial than the control condition. When an interaction is found, we will look at whether there is a significant difference between PRE and F4 in each group and assess group differences on change scores at post-training ([PRE – F4]/|PRE|). Efficacy is supported if the F4 change score is larger in the intervention group than in the control group. All analyses will be adjusted for site and baseline performance.

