A similar approach will be taken for most of our secondary objectives. A set of secondary objectives of the study is to assess the long-term maintenance of the effect of the training. This will use a mixed linear model to test long-term maintenance of intervention effects (PRE versus F24) on primary outcome, as well as separate models (with three levels of time: PRE, F4, and F24) on measures of attentional control, psychological health variables (anxiety/depression, apathy, quality of life, help seeking), everyday functioning measures (MMQ, AMQ, ADCS-ADL-PI, the Cognitive Activities Questionnaire, Memory Toolbox, and DAFS-R), and on the structural brain measures (hippocampal volume and cortical thickness). Because the Jessen questions about subjective complaint are dichotomous, Chi-square analyses will be used to compare the number of participants who have a memory complaint before and after the intervention as a function of condition. For exploratory purposes and to inform future interventions, the above analyses will be repeated comparing the music and Spanish arms. The *p* values will be presented before and after adjustment for multiple comparisons based on the Hochberg procedure. All statistical tests will be two-tailed and a *p* value of less than 0.05 will indicate statistical significance. All computations will be made with SPSS version 23.0 (SPSS Inc., Chicago, IL, USA).

Functional MRI data will be subjected to standard pre-processing steps using SPM8 (i.e., motion correction, slice timing correction, co-registration with anatomical T1 image, spatial normalization). First level (individual) analyses will involve general linear models with box-car responses, convolving the time course of the event-related response per condition with the canonical hemodynamic response function. Second level (group) analyses will treat participants as a random variable, with each contrast tested at *p* < 0.05 after whole-brain, family-wise error correction. A cluster threshold of 50 or more contiguous voxels will be applied.

Preliminary analyses of the descriptive characteristics and baseline performance will be done after full recruitment is completed. Analysis of efficacy will be done at the end of the 4-month follow-up and long-term analyses will be done at the end of the 24-month follow-up.

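### The exploratory comprehensive-cohort comparison of music with Spanish is confounded by which activity participants excluded, because the stated model has no term for that choice

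*Protocol article*

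**What the plan says.** All places are in the protocol article.

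- **Objectives and hypotheses:** "the study will examine whether music and Spanish lessons produce different effects on the primary and secondary outcome measures".
- **Randomization and blinding procedure:** "The opportunity to exclude either music or Spanish training will be offered to all participants prior to randomization". The first allocation is intervention versus control: "This will be done with a 2 to 1 ratio between intervention and control conditions". Within the intervention arm the second allocation is random only for some, "using a 1 to 1 ratio for participants who did not exclude either of these two activities". For the others, "Participants randomized in the intervention condition who excluded music or Spanish training will be placed in their preferred activity".
- **Design (text below Fig. 1):** intervention versus control is fully randomised, but "secondary analyses comparing the two leisure activities will rely on a partially randomized cohort".
- **Analysis of efficacy and maintenance on primary and secondary outcomes:** randomised participants are analysed first. Then, "This will be followed by analyses of the comprehensive cohort which will include those in the preference arms". The fixed effects are intervention, time and their interaction, with adjustment for site and baseline performance. For exploratory purposes and to guide later interventions, "the above analyses will be repeated comparing the music and Spanish arms".

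No term for the excluded activity appears in this section or among the moderators listed under Analysis of moderators.

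**The concern.** The question is whether the two kinds of lesson have different effects. Among excluders, lesson and exclusion choice coincide completely, so their data cannot separate the two. If people who reject Spanish and people who reject music differ in practice effect, decline or engagement, that difference enters the arm-by-time term. Adjusting for baseline performance removes a difference in starting level but not a difference in change.

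The article's own reason for allowing exclusions (Design; Adherence to treatment and retention) is that preference affects motivation, engagement and adherence, so a difference in change is not far-fetched. At stake is an analysis that uses more participants than the randomised-only one, looks more precise, and could show a music-Spanish difference when the lessons work equally well. The article does not say which of the two results governs if they disagree.

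**Working it through.** **Inputs from the article.** 144 participants, 2 to 1 allocation, 18% attrition, two-sided 0.05. Trained: 144 × 2/3 = 96, and 96 × 0.82 = 78.7 completers. Control: 48 × 0.82 = 39.4 completers. The article gives no planned figure for music versus Spanish, so there is none to reproduce.

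**Assumed, because the article does not give them.** Let e be the total share excluding an activity, split evenly between the two. Let D be the difference in change between Spanish-excluders and music-excluders, with non-excluders midway. The SD of change is 1, and the lessons have identical effects.

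**Bias.** Each activity group is then a share (1 − e) of randomised non-excluders and a share e of placed excluders. Music is shifted by +e × D/2 and Spanish by −e × D/2, so:

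estimate = lesson difference + e × D

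**Rejection rate.** SE = √(1/39.4 + 1/39.4) = 0.225. The rate is Φ(e·D/SE − 1.96) + Φ(−e·D/SE − 1.96). For e = 20% and D = 0.5, the bias is 0.10 and 0.10/0.225 = 0.444. The rate is Φ(−1.516) + Φ(−2.404) = 0.065 + 0.008 = 7.3%.

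| Total excluding (each activity) | D = 0.3: bias, formula, simulated | D = 0.5 | D = 0.8 |
|---|---|---|---|
| 20% (10%) | 0.06, 5.8%, 5.5% | 0.10, 7.3%, 7% | 0.16, 10.9%, 10% |
| 40% (20%) | 0.12, 8.3%, 8.6% | 0.20, 14.4%, 13% | 0.32, 29.5%, 28% |
| 60% (30%) | 0.18, 12.6%, 11% | 0.30, 26.5%, 25% | 0.48, 56.7%, 53% |

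The formula runs slightly high at the large values because it ignores the extra spread that the excluder difference adds within each group. An uneven split changes little: at e = 50% and D = 0.5, a 3 to 1 split gives a bias of 0.233 and 17.1% rejection, against 0.25 and 19.8% for an even split.

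**Does the contrast still respond to the lessons?** Yes. In a large simulated data set with a true lesson difference of 0.5 SD and no excluder difference, the model without the term returned 0.51.

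**What an exclusion term does.** In music and Spanish participants alone it reproduces the randomised-only estimate (simulation: −0.043 for both, true value 0, against 0.193 without the term). Excluders then add nothing. Information is gained only when ENGAGE-DISCOVERY participants, who also stated their exclusions, are in the model. They show how each kind of excluder changes without either lesson.

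| Each activity excluded by | SE, randomised only | SE, exclusion term with controls |
|---|---|---|
| 10% | 0.253 | 0.244 |
| 20% | 0.294 | 0.266 |
| 30% | 0.362 | 0.295 |

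The unadjusted comprehensive SE is about 0.226.

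If the excluder difference is the same in trained and control participants, the adjusted model rejects in about 5%. If a 0.8 SD difference arises only under training, the adjusted model stays biased by about 0.05, 0.14 and 0.27 SD at 10%, 20% and 30% excluding each activity. It then rejects in about 6%, 8% and 15%, while the randomised-only analysis stays near 5%.

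**The case against.** The plan already runs the unconfounded comparison, and runs it first. It calls the activity comparison exploratory and only partially randomised. The comprehensive result is a declared supplement, and the exact covariates of such a model are often left to a fuller document.

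Most of this stands and limits the weight of the point. It does not remove it: the article does state a model and a covariate set for all analyses, and then says that they are repeated for music versus Spanish. Acknowledging partial randomisation does not change what the model estimates.

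A second objection is that the large rejection rates rest on strong assumptions. Exclusion is offered for strong dislike, so few may use it. A D of 0.5 or 0.8 SD would make the choice of excluded activity matter about as much as the medium and large training effects cited from the pilot. That stands too: at 20% total exclusion and 0.3 SD the rate is only about 5.5%.

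A third is that controls cannot reveal engagement with a lesson they never receive, so the adjusted model is no complete cure. That is also correct.

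**Conclusion.** The comprehensive-cohort music-Spanish estimate is confounded by exclusion choice. Its bias is the share excluding times the excluder difference in change. Under assumed values this is negligible if few exclude (about 7% rejection at 20% total and 0.5 SD). It is material if many do (about 25% at 60% total and 0.5 SD, about 11% at 60% and 0.3 SD). The article gives no figure that would place the trial in this range.

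A reader might go further in three ways that the article does not support:

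- That the analysis compares types of excluder and says nothing about the lessons. It mixes randomised and placed participants and does respond to a true lesson difference. Only if everyone excluded an activity would no randomised information remain.
- That the trial's main result is compromised. Intervention versus ENGAGE-DISCOVERY is fully randomised, with exclusions stated beforehand, and the randomised-only music-Spanish comparison is sound.
- That an exclusion term always restores the 5% level. It does so only if lesson effects, including engagement with the lesson, do not depend on the exclusion choice.

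This is worth correcting, in proportion to an exploratory analysis.

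**What to change.** 1. State that any conclusion on music versus Spanish rests on the randomised-only comparison.
2. For the comprehensive-cohort analysis, fit all randomised participants in three arms (music, Spanish, ENGAGE-DISCOVERY). Add the pre-randomisation exclusion choice (none, music, Spanish) and its interaction with time, and take the music-minus-Spanish-by-time contrast.
3. State the assumption named in the verdict beside that result.
4. Report the number excluding each activity, by arm.

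No new data are needed, since the choice is made by all participants before randomisation. The cost is a wider SE than in the unadjusted comprehensive analysis, for example 0.27 against 0.23 SD at 20% excluding each activity. If few exclude, the gain over the randomised-only analysis is small: 0.244 against 0.253 at 10% each, about 4%. With about 39 control completers, that scenario rests on roughly four controls of each excluder type (39 × 0.10).

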#### Analysis of moderators

A small set of time-invariant variables will be included as predictors to assess their effects on primary and secondary outcomes. Three pre-specified subgroup analyses will be done according to sex (male versus female), education (less versus more than 12 years), and age (younger versus older than 75 years at baseline). Other subgroup analyses will be exploratory, such as reserve score based on the adapted version of the Rami and colleagues cognitive reserve questionnaire [32, 49], genetic markers of brain plasticity and risks for dementia (APOe4, BDNF, and COMT), baseline brain structure and function, depression (BDI-II [47]), and anxiety (BAI [48]). We will also include the expectations of participants regarding the cognitive training, compliance with the intervention (percentage of sessions attended and percentage of homework completed), amount of knowledge acquired during the intervention, and self-efficacy perception (personality measures). Stepwise regression analyses with the per-protocol participants from the cognitive training group will be used to explore whether the moderators predict delayed memory change scores at the two follow-up time points.

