**Methods:**

One hundred and forty-four older adults with a memory complaint will be recruited in Montreal and Toronto. A particular effort will be made to reach persons with low cognitive reserve. Participants will be randomly assigned to one of two conditions: cognitive + leisure training (ENGAGE-MUSIC/SPANISH) or active control (ENGAGE-DISCOVERY). The ENGAGE-MUSIC/SPANISH training will include teaching of mnemonic and attentional control strategies, casual videogames selected to train attention, and classes in music or Spanish as a second language. The ENGAGE-DISCOVERY condition will comprise psychoeducation on cognition and the brain, low-stimulating casual videogames and documentary viewing with discussions. To retain the leisure aspect of the activities, participants will be allowed to exclude either music or Spanish at study entry if they strongly dislike one of these activities. Participants randomized to ENGAGE-MUSIC/SPANISH who did not exclude any activity will be assigned to music or Spanish based on a second random assignment. Training will be provided in 24 2-h sessions over 4 months. Outcomes will be measured at baseline, at 4-month follow-up, and at 24-month follow-up. The primary outcome will be cognitive performance on a composite measure of episodic memory (delayed recall scores for words and face-name associations) measured at baseline and at the 4-month follow-up. Secondary outcomes will include a composite measure of attention (speed of processing, inhibition, dual tasking, and shifting), psychological health, activities of daily living, and brain structure and function and long-term maintenance measured at the 24-month follow-up. Information on cognitive reserve proxies (education and lifestyle questionnaires), sex and genotype (apolipoprotein (Apo)E4, brain-derived neurotrophic factor (BDNF), and catechol-O-methyltransferase (COMT)) will be collected and considered as moderators of training efficacy.

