This study will be the first to test the efficacy of an intervention that combines leisure-based and formal cognitive training approaches. It will also address important knowledge gaps regarding cognition-focused interventions in the current scientific literature. The first critical issue is the lack of evidence that cognitive training improves activities of daily life [24]. Indeed, most training studies have failed to measure transfer or reported limited context transfer, defined as cognitive improvement carried over into an environment different from the one where training occurred [25, 26]. The lack of context transfer might be due to the fact that participants have difficulties applying the newly learned strategies from the classroom context to more complex situations encountered in their daily life. Notably, context transfer can be improved by training participants to apply the learned strategies in varied and more ecologically valid situations [12]. Thus, an additional advantage for including leisure activities is that they provide the opportunity to apply the different strategies learned during formal cognitive training to situations encountered during the music and Spanish sessions, and while playing videogames. For example, semantic association strategies will be used to learn Spanish vocabulary. Thus, the leisure sessions will offer an ecologically valid setting for participants to use and practice their strategic skills. It is anticipated that reinforcing and broadening strategy use will make participants more likely to employ them in other contexts within their everyday life. Another innovative aspect of the study will be to investigate individual differences in response to cognitive training. Very little is known about the characteristics that identify who will benefit the most from an intervention. The study will analyze the effect of a small set of variables (education, age, sex) that may be associated with differences in gains from training based on prior findings. As participants will be deeply phenotyped, it will also be possible to assess the effects of other variables on an exploratory basis (e.g., baseline brain structure and function, health). The study will also measure the effect that cognitive training has on brain structure and function. A few studies have shown that cognitive training in persons with MCI may lead to greater brain activation and increased structural connectivity [27, 28]. However, researchers still have a very limited understanding of how these interventions alter brain structure and function in older adults, whether these effects are long-lasting, whether the characteristics of participants contribute to these brain changes, how structural and functional changes relate with one another, and whether training gains depend on specialized brain regions or involve neurocompensatory responses from alternative regions.

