This study has many strengths. One of them is the inclusion of an active control condition and strategies used to reduce and control for the expectation effects of participants. The majority of intervention studies use a no-contact or wait-list control group comparison, a design that does not allow control for the effects of social stimulation, expectations, or additional stimulation from everyday routine. By including an active control condition that mirrors the structure and the level of social engagement of the intervention condition, while providing the same expectations in terms of potential benefits, this study is in a better position to confidently attribute any positive results to the content of the program. This study will also measure generalization of cognitive benefits to everyday tasks, which is an important indication of the impact of the intervention. Furthermore, the study includes a number of approaches to increase transfer to activities of daily living, for instance practicing the cognitive strategies during the leisure sessions and including homework for practice in the home environment of participants. It will also measure the neural substrates of training-related benefits by using MRI and fMRI, which will contribute to building knowledge on the brain mechanisms by which such interventions exert their effects. Finally, few studies have assessed the long-term effect of cognitive interventions up to more than a year after training and, thus, the 24-month assessment included here will provide critical information on the maintenance of the effects as well as their impact on cognitive decline.

An important component of this study is to enroll participants with limited education to compare training efficacy as a function of cognitive reserve proxies. This is critical because cognitively stimulating interventions might be particularly beneficial to those individuals who are at greater risk of developing dementia. Furthermore, results will be more representative of the general population and hence more generalizable. Finally, as the population will be well characterized, it will be possible to assess whether some genetic, cognitive, or demographic characteristics are associated with a better response to treatment. This will allow provision of recommendations for the type of older adult who is most likely to benefit from such intervention.

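### The protocol asks whether sex, age and education change the training effect, but the moderator section states predictor and subgroup analyses and names no characteristic-by-intervention test

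*Protocol article*

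**What the plan says.** Most of the article poses a moderation question. The abstract's Methods paragraph says that reserve proxies, sex and genotype "will be collected and considered as moderators of training efficacy". The Background announces that "The study will analyze the effect of a small set of variables (education, age, sex", and ties this to differences in training gains. Under Objectives and hypotheses the hypothesis is that "we hypothesize that participant characteristics (sex, age, education) will modulate efficacy and transfer". The objective sentence in the same section is looser: "to identify if the characteristics of participants modulate outcomes".

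The section Analysis of moderators then states the method: "A small set of time-invariant variables will be included as predictors to assess their effects on primary and secondary outcomes". It goes on: "Three pre-specified subgroup analyses will be done according to sex (male versus female), education (less versus more than 12 years", and also by age, split at 75 years. It ends with an exploratory stepwise regression among per-protocol participants of the training group.

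The efficacy section lists intervention, time and their interaction as the fixed effects, and adjusts all analyses for site and baseline performance. No interaction between a characteristic and the intervention, and no test of the difference between subgroup effects, is named anywhere in the article.

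The Discussion says of this work: "This will allow provision of recommendations for the type of older adult who is most likely to benefit from such intervention".

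**The concern.** A characteristic moderates training if the intervention-versus-control gain differs across its levels. It is prognostic if it goes with better or worse memory in both arms alike. The stated target, the characteristics' effects on outcomes, is the second of these. Education or age may predict memory well and still have no bearing on who gains from training.

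Subgroup analyses do not close the gap unless the subgroup effects are compared directly. Each stratum holds only part of a modest sample, so one can reach p < 0.05 and the other miss it when the true effects are equal.

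At stake is a secondary objective and the stated wish to say which older adults should be offered the programme. Neither a main effect nor a pair of stratum results can support such advice.

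**Working it through.** **Inputs from the protocol.** 144 participants and 18% attrition (Sample size); 2:1 allocation (Randomization and blinding procedure); two-sided 0.05. Completers: 96 x 0.82 = 79 intervention and 48 x 0.82 = 39 control, 118 in all.

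**Inputs assumed, because the article gives none.** Standardised effect d from 0.3 to 0.8 (the text says only medium and large), stratum splits of 50:50 and 30:70, and the correlations below. The article gives no power and no numeric effect size (it refers to an appendix), so 144 cannot be reproduced. The point does not depend on it.

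**1. What each stated analysis estimates.**
- Characteristic as predictor of outcome: a difference in outcome between, say, education groups, with the arms pooled. It does not compare arms.
- Subgroup analysis: an intervention effect in each stratum. It compares arms within a stratum, but strata are compared only if a test of the difference is added.
- Characteristic x intervention x time: the difference in training effect between strata. This is the hypothesis, and it is not named.

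**2. Strata that disagree when the true effects are equal.** Power in a stratum holding share s is Φ(d / √(1/(39s) + 1/(79s)) − 1.96). For s = 0.5 and d = 0.5 the standard error is √(1/19.5 + 1/39.5) = 0.277, and power is Φ(1.81 − 1.96) = 0.439. The chance that exactly one stratum is significant is p1(1 − p2) + p2(1 − p1) = 2 x 0.439 x 0.561 = 0.493.

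| d | 50:50 split | 30:70 split |
|---|---|---|
| 0.3 | 31% | 32% |
| 0.5 | 49% | 53% |
| 0.6 | 49% | 55% |
| 0.8 | 29% | 41% |

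A simulation at d = 0.5 (4,000 trials per setting) gave 49% to 54%. In the same trials the characteristic-by-intervention test rejected in 4.7% to 5.4%.

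**3. Predictor route, with the stated baseline adjustment.** Suppose a characteristic correlates r = 0.3 with memory at both visits and does not moderate training, and that baseline and 4-month memory correlate ρ. The partial correlation with 4-month memory given baseline is r(1 − ρ) / √((1 − r²)(1 − ρ²)). The rejection rate is about Φ(atanh(partial) x √(118 − 4) − 1.96).
- ρ = 0.5: partial = 0.15 / √(0.91 x 0.75) = 0.182; 0.184 x 10.68 = 1.96; rate about 50%.
- ρ = 0.6: partial 0.157; about 40%.
- ρ = 0.7: partial 0.132; about 30%.
- ρ = 0.8: partial = 0.06 / √(0.91 x 0.36) = 0.105; 0.105 x 10.68 = 1.12; about 20%.

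If the characteristic instead shifts change over time by 0.2, 0.4 or 0.5 SD equally in both arms, simulation gives 18%, 57% and 77% (50:50) or 16%, 48% and 68% (30:70). With no effect on change the rate is about 5%, so this route misleads only when the characteristic is prognostic.

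**4. Power of the right test.** The overall effect has standard error √(1/79 + 1/39) = 0.196, so 80% power needs (1.96 + 0.84) x 0.196 = 0.55 SD. With a 50:50 split the interaction's standard error is 0.277 x √2 = 0.391, and 80% power needs a difference between strata of about 1.10 SD.

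**The case against.** The best defence is that a condensed article need not write out every model term. The section is headed as an analysis of moderators, and adding time-invariant variables as predictors is ordinary mixed-model language. Most secondary objectives are also said to follow an approach like the efficacy analysis, which looks at an interaction first. A full analysis plan could supply the missing term.

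That stands in part. The absence of a formula alone would be no finding. But the section does more than omit: it gives the variables a role (predictors) and a quantity (their effects on outcomes), and that quantity is not the one hypothesised. An analysis plan that followed the sentence faithfully would test the wrong thing.

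Two stronger readings are tempting and should be resisted. A reader might infer that the intervention will be tested separately within each stratum and moderation declared from discordant p values. The article says only that subgroup analyses will be done; these can be run through an interaction. A reader might also take the raw correlation of 0.3 with 118 completers and conclude that the predictor test is almost bound to be significant. That ignores the stated adjustment for baseline performance, which brings the rate down to the 20% to 50% shown above.

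Two further points temper the concern. The objective sentence speaks only of modulating outcomes, so the article is not uniform in posing a moderation question. The Discussion sentence about recommendations is an aspiration and does not say which analysis would support it.

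**Conclusion.** The concern holds as a mismatch between question and stated analysis. The abstract, Background and hypothesis ask whether characteristics change training efficacy. The moderator section states an analysis of their effects on outcomes plus subgroup analyses, and no test of differential effect is named. Taken literally, the predictor analysis is prognostic, and subgroup results without an interaction test cannot show who is most likely to benefit.

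The size is conditional. The disagreement rate of about 30% to 55% per factor, against about 5% for an interaction test, applies only if moderation is judged by significance in one stratum and not the other. The 20% to 50% for the predictor route assumes a correlation of 0.3 at both visits and a baseline to 4-month correlation between 0.5 and 0.8. Both rest on 79:39 completers.

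The primary efficacy comparison is not affected. The correction should be made before the moderator results are analysed.

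**What to change.** In Analysis of moderators, replace the sentence on predictors with a statement along these lines:
- Moderation by sex, education and age is tested, one characteristic at a time, by the characteristic x intervention x time term, with its lower-order terms, added to the efficacy mixed model and fitted in both randomised arms. It is reported as an estimate with a 95% CI.
- Stratum-specific training effects come from that same model and are descriptive.
- Main-effect results for a characteristic are labelled prognostic and are not evidence of differential benefit.

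No new data are needed; this is a change of wording. The price is low power: with an even split, only a difference between strata of about 1.10 SD would be found with 80% power. Intervals will therefore be wide and fewer moderation claims possible. The Discussion's aim of recommending the programme to particular groups should be worded with that in mind.
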